#### Phase 3. Development and usability testing of DigiDOL-Ad and accompanying websites

2.2.3

In this phase, DigiDOL-Ad and the accompanying websites will be developed. Psychologists with extensive experience in the treatment of adolescents with chronic pain, a software engineer and a graphic designer, all with wide experience in the development of health applications [e.g., (23, 28–30)], will develop DigiDOL-Ad and the websites, leveraging the data obtained in earlier phases. In this process, we will use the *mHealth assessment and development guideline* [MAG; (24, 31, 32)] to help guide the development and ensure that DigiDOL-Ad meets the expected safety, security, privacy, usability, transparency, appropriateness and usability requirements for a health app. This treatment will have a psychosocial focus. Drawing from our prior development of digital treatments [e.g., (30)], we anticipate that the duration of the current intervention will be approximately 8 weeks. Importantly, DigiDOL-Ad will be designed to be a stand-alone intervention. That is, adolescents with chronic pain will not have the option to interact with a therapist (or with other adolescents) and the treatment itself will be self-guided as we have already implemented in previous apps with significant positive results (23, 28, 30). The digital treatment will be developed on data-driven clinical guidelines, such as World Health Organization's guidelines (12) on the management of chronic pain in children. The application will be developed for both the Android and iOS platforms to ensure widespread accessibility. Furthermore, its potential integration into the Spanish healthcare system will be explored.

A website for parents and a website for teachers will be also developed as companions to DigiDOL-Ad. The objective is that both parents and teachers act as active change agents to help adolescents with chronic pain improve. The content of the parents' web page will be based on the adolescent's treatment and will provide suggestions on what to do and not do to support adolescents in progressing though the treatment. Given that adolescents spend a significant portion of their time at school and the critical role it plays in their overall development, we will also develop a website for teachers. This website will provide resources and information to support students with chronic pain. The content will be based on the information gathered with the FGs with teachers and will be aimed at providing practical resources, strategies, and information tailored to the school setting. The general idea is that the content should empower teachers to understand, accommodate, and assist students while fostering an inclusive and supportive learning environment.

The usability study of DigiDOL-Ad will be conducted with groups of adolescents with chronic pain and is based on the concept of a “hermeneutical circle”. This involves an iterative process of implementing a design, gathering insights through discussions and feedback, and refining the design in successive cycles until it becomes user-friendly and minimizes errors. Based on previous experiences (23, 33), we expect that 2–3 cycles will be required, with each session taking about 45 min. Participants in these tests will be informed of the purpose, procedures, risks, and asked to sign an informed consent or assent to participate (see Supplementary Appendix 2 for a copy of the consent/assent forms to be used in this study). Participants will engage with DigiDOL-Ad using only the standardized instructions embedded within the app, as it is designed to be self-explanatory and guide users independently through the content. A “concurrent thinking” protocol will be employed, during which participants' actions will be observed, and detailed field notes will be recorded and transcribed. Errors made during app usage will also be documented. Following the completion of the assigned tasks, participants will respond to open-ended questions regarding the app's usability, efficiency, and overall satisfaction, based on methodologies established in prior comparable studies (30).

#### Phase 4. Evaluation study of DigiDOL-Ad

2.2.4

In this last phase, we will evaluate DigiDOL-Ad. This will be a multi-site study with 8 hospitals referring potential participants. The procedure will begin with adolescents and their parents responding to a battery of questionnaires. This assessment will be conducted online, to decrease biases due to social desirability effects. We will use the *REDCap System* (34) to implement the online assessment, which allows for programing follow-ups at the different data collection points. Participants will be assessed three times: Pre- and Post-treatment (T1, T2) and 3-months follow-up (T3, adolescents only). After completing T1 assessment, participants will receive access to DigiDOL-Ad (adolescents) and to the webs (parents and teachers).

Participants will receive written instructions detailing how to access the treatment. Each participant will be assigned a unique username and password, which will be linked to their participant ID. This linkage will facilitate the monitoring of participants' adherence.

To maximize retention of participants the project will simplify accessibility and provide easy-to-understand instructions for downloading, accessing, and using the app. In addition, reminder emails with personalized and motivational messages will be sent at each assessment point. Moreover, we will conduct periodic surveys or check-ins every week to identify barriers to participation, such as time constraints or usability issues, and participants will receive compensation for completing the surveys. In addition, to maximize engagement from the healthcare professionals, they will receive information on the study progress and preliminary findings -when possible- using periodic newsletters to sustain interest. Moreover, they will be informed about the referral and enrolment volumes per hospital, emphasizing the value of their contribution to the study and its potential impact on improving chronic pain management in adolescents. Importantly, the project will acknowledge participants' efforts through individual thank-you notes and public acknowledgment in study updates. Finally, the project will build trust and rapport by facilitating transparent communication with a study coordinator to build a personal connection with participants.

In the check-ins mentioned earlier, open-ended questions will be included, to allow participants to report any unintended effects of the intervention and identify potential causes. This feedback will facilitate necessary improvements to the intervention. All collected information will be securely stored on the same servers as the other study data.

To ensure transparency and compliance, any important protocol modifications in the research project will be communicated promptly and appropriately to all relevant parties. Our plan outlines the steps, responsibilities, and channels for effectively disseminating such changes to: (a) research team members (i.e., immediate notification followed by detailed discussions in the next scheduled meeting and revised protocol documents shared via secure project management platforms); (b) research ethical committee (i.e., formal submission of an amended protocol along with supporting documentation including a rationale for changes and a complete risk assessment); (c) participants (i.e., direct communication via email, app notifications, or phone calls, depending on participant's preference); (d) trial registry (i.e., update clinical trial registry records to reflect modifications). Moreover, we will maintain a log of protocol modifications, communication records, and acknowledgments from all parties, and store updated documents in a centralized and secure location accessible to the research team.

We plan to disseminate the project's results, targeting both general audiences and specialized groups. This will include social media and communication through patient associations. Likewise, we will share the findings in scientific forums like specialized scientific journals, meetings and congresses. Additionally, we will send email updates to all the stakeholders that participated to ensure transparency and broad accessibility to the outcomes.

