In this study, the sample will include adolescents with chronic pain and one of their parents. Based on a within-subjects repeated measures ANOVA with three time points (baseline, post-treatment, and 3-month follow-up), we will use GPower (version 3.1.9.7) to calculate the required sample size. We set a small effect size (f = 0.10), with a two-tailed alpha of 0.05 and power of 0.80. For the calculation, the following parameters were assumed: number of measurements = 3 (baseline, post-treatment, and 3-month follow-up), correlation among repeated measures = 0.5, and nonsphericity correction epsilon = 1. This calculation indicated that a sample of *N* = 163 dyads would be sufficient. However, in order to prevent attrition issues, we will be recruiting a minimum of 195 dyads -minimal attrition is expected based on prior studies on digital treatments with similar populations (37). Recruitment is expected to proceed at a rate of approximately 5 participants per month, based on projections from similar previous studies [e.g., (30)]. To account for potential variability, we conservatively estimate a recruitment rate of 2 adolescents per month per hospital. With 8 hospitals participating, this would result in enrolling the required sample of 352 participants within 22 months. An additional 5 months will be allocated for participants to complete the treatment (approximately 8 weeks, as previously described) and the 3-month follow-up, bringing the total duration for recruitment, enrollment, and follow-up to 27 months.

In order to ensure that the target sample size is reached in the evaluation study, the following strategies will be implemented: (a) using clear and engaging messages (i.e., developing age-appropriate, visually appealing recruitment materials, like posters, flyers, or videos to be shared by hospitals and healthcare professionals); and (b) highlighting the benefits of participation, such as improving their own pain management and contributing to advancements in adolescent healthcare. Moreover, we will offer both monetary and non-monetary incentives (i.e., certificates of participation and feedback on their progress). To enhance participant retention and ensure completion of follow-ups, we plan to implement personalized reminders. These reminders will be delivered via app notifications, SMS, or email, and will serve to notify participants of upcoming tasks or scheduled follow-up activities.

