### Limitations

3.2

The key challenges anticipated in this project are related to (1) recruitment and inclusion of participants in the different studies, due to abandonment of a clinician/chronic pain program, and the difficulty to involve stakeholders in the FGs and usability studies; (2) privacy and data protection issues; (3) as a digital intervention, potential technical difficulties or poor usability could affect participants engagement; and (4) the content on companion websites for parents and teachers might be misunderstood, leading to unintended consequences. The mitigation actions (*contingency plan*) addressed to solve recruitment issues are as follows, depending on the causes: (a) monitoring constantly the involvement of clinicians, having a close and continued relationship with them (in relation to this, we have planned to send monthly updates to clinicians, and award a prize to the program providing the highest number of referrals), and (b) the Principal Investigator, in ongoing meetings with all stakeholders, will inform them on the project to raise interest and gain trust in the outcomes of the research proposal. In relation to (2) privacy data issues, we plan that the data collected during the implementation process will not leave the local secure networks where the data will be hosted at the university premises. Moreover, in relation to technical and usability issues, we have planned iterative usability testing phases and will provide dedicated technical support to identify and resolve any issues promptly. Finally, in relation to misinterpretation of information, the content will be developed in consultation with experts, and clear guidelines for interpretation and use will be provided.

Finally, another limitation of this project is the use of a single-group design to study the treatment. Without a control group for comparison, it is challenging to determine whether the observed outcomes are genuinely attributable to the treatment or influenced by external factors such as the placebo effect, natural progression of the condition, or other variables. If the evaluation study demonstrates positive results, a randomized controlled trial will be conducted in the future to validate and strengthen the findings.

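### Preliminary findings may go to referring clinicians while recruitment and follow-up are still open, with no embargo on outcome data, in a single-group study with self-reported main outcomes

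*Protocol article*

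**What the plan says.** In the Phase 4 section (2.2.4) the evaluation is described thus: "This will be a multi-site study with 8 hospitals referring potential participants". The same section turns to keeping healthcare professionals engaged and says "they will receive information on the study progress and preliminary findings -when possible- using periodic newsletters to sustain interest". The next sentence adds that "they will be informed about the referral and enrolment volumes per hospital, emphasizing the value of their contribution to the study". The Limitations section (3.2), as a remedy for slow recruitment, states "we have planned to send monthly updates to clinicians, and award a prize to the program providing the highest number of referrals".

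For participants, the Participants section (2.3) lists "non-monetary incentives (i.e., certificates of participation and feedback on their progress". It does not say what that feedback contains or when it is given.

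The main outcomes (section 2.4) are pain intensity, pain interference and global impression of change, all completed by the adolescents. The Limitations section acknowledges that "another limitation of this project is the use of a single-group design to study the treatment", and that placebo effects and natural course therefore cannot be ruled out. It does not name the release of interim findings as a source of bias.

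**The concern.** Outcome results from a running study are normally withheld from those who can still influence who enters it and what entrants expect. Here the article commits to the opposite, with only a practicability qualifier.

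Two things could shift. Clinicians who learn that the app seems to help, or helps a certain kind of patient, may refer later patients selectively. They may also pass their optimism to families. In a controlled trial both arms would share such shifts. In one group measured before and after treatment they become part of the observed change.

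Global impression of change raises a related issue. It asks the adolescent to judge their own improvement. If the feedback offered as an incentive reports symptom scores before that rating is made, it could supply the answer. At stake is how far a positive result can be read as an effect of the app, and the Limitations section makes a later randomised trial conditional on positive results.

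**Working it through.** No effect estimate is involved. The check is whether findings could reach referrers while they are still referring, and by what route that could affect the outcomes.

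**1. Recipients.** The newsletters carry referral and enrolment volumes per hospital, which are of use mainly to the referring side. The monthly updates are addressed to clinicians as a recruitment measure and sit beside a prize for referrals. The recipients therefore include the people who refer.

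**2. Timing.** The article gives no dates for the newsletters, but sustaining interest and reporting enrolment only make sense during recruitment. Inputs from sections 2.2.3, 2.2.4 and 2.3: 8 hospitals, 2 adolescents per hospital per month, treatment of about 8 weeks, follow-up 3 months later, a minimum of 195 dyads, and elsewhere in section 2.3 a required sample of 352.

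- Planning rate: 8 × 2 = 16 per month.
- The article's own figure: 352 / 16 = 22 months, which reproduces. Adding 5 months for treatment and follow-up gives 27, as stated.
- For the 195 target: 195 / 16 = 12.2 months.
- First T2 result at about month 2; first T3 result at about month 2 + 3 = 5.

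| Sample | Recruitment | Still open after first T2 | Still open after first T3 |
|---|---|---|---|
| 195 | 12.2 months | 12.2 − 2 = 10.2 | 12.2 − 5 = 7.2 |
| 352 | 22 months | 22 − 2 = 20 | 22 − 5 = 17 |

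At month 5, with even accrual and no attrition, 16 × 3 = 48 adolescents would have passed T2, and 195 − 16 × 5 = 115 of the 195 would still have to be referred.

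The article also mentions about 5 participants per month without saying whether that is per hospital. If it is overall, recruitment of 195 lasts 195 / 5 = 39 months and the overlap is longer. If it is per hospital, recruitment lasts 195 / 40 = 4.9 months. The overlap after the first T2 is then about 2.9 months, and recruitment closes at about the time of the first T3. Some overlap exists on every reading.

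**3. Route to the outcomes.** The planned analysis is a within-subject repeated-measures ANOVA (sections 2.3 and 2.5). A stable difference between adolescents referred early and late cancels in each adolescent's own change, so a different case mix does not by itself bias the result. Bias needs a factor that alters change: selection of likely responders, higher expectation, or referral at a temporary peak of pain followed by regression to the mean. Interim findings could plausibly influence the first two. Global impression of change has no T1 value, so a stable tendency to answer favourably is not differenced out of it.

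**4. Existing safeguards.** Assessment is online, to reduce social desirability, and treatment expectancies are measured in adolescents and parents (section 2.4). Neither limits what clinicians are told.

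**The case against.** The case against has weight. Clinicians neither deliver the treatment nor rate the outcomes. Section 2.2.3 describes a self-guided app with no therapist contact, and section 2.3 has hospital representatives hand out brochures, after which families contact the research team. Release is qualified by practicability, and preliminary findings might mean usability or retention rather than outcomes. Expectancies are measured and could be related to change. The article presents the study as a step before a randomised trial and discloses the single-group limitation. All of this stands, and it makes the route indirect and the likely effect modest. It does not remove the point: releasing preliminary findings is a stated practice, not a detail left to a fuller protocol. Measuring expectancy in one group does not separate its effect from that of treatment.

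Three stronger readings are tempting and not supported.

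- A reader might infer that participants will see their symptom scores before T2 or T3. The text settles neither content nor timing. The feedback is listed beside certificates of participation and may mean progress through the programme.
- A reader might fault the plan for recruiting by "highlighting the benefits of participation, such as improving their own pain management". Mentioning possible benefit is ordinary recruitment language, no actual recruitment text is shown, and the consent procedure, which describes procedures and risks, has ethics approval. Asking for other wording would be a preference.
- A reader might size the problem by assuming a reporting shift and computing how often it would give a significant result. Nothing in the document ties any shift to newsletters or feedback. The same figures would arise from any drift in any single-arm study, which is the weakness already disclosed.

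**Conclusion.** The point holds in a limited form. The article commits to sending preliminary findings to the referring side and states no embargo, and on its own timetable outcome data would exist during recruitment: for about 7 to 10 months at 16 per month and 195 dyads, and longer if 352 are enrolled. In an uncontrolled study with self-reported main outcomes, this is an avoidable source of selective referral and raised expectation. The size of any bias cannot be estimated from the document, and the finding does not imply that results would be invalid.

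The conclusion rests on two assumptions: that the newsletters go out while referral is open, which is the natural reading though not stated literally, and that preliminary findings can include outcome data, which the text does not exclude. The participant-feedback part is conditional: it applies only if the feedback includes symptom or outcome scores and comes before that adolescent's T3.

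**What to change.** State in the Phase 4 section that newsletters and monthly clinician updates contain only enrolment, referral and retention counts, and that no outcome data are released to sites until the last T3 assessment is complete. Apply the same limit to the stakeholder meetings mentioned under Limitations.

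In the Participants section, say what the progress feedback consists of. If it includes symptom or outcome scores, give it only after that adolescent's own T3, so that it cannot inform the global impression of change. Feedback on programme completion can remain as planned.

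The cost is wording and timing only; sample size, assessments and analysis do not change. Newsletters become slightly less engaging for referrers, although recruitment counts and recognition of each hospital's contribution remain available to sustain interest.

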### Participants

2.3

For adolescents interested in participating, they must meet the following *inclusion* criteria: (1) being between 12 and 18 years of age; (2) having a non-oncology secondary chronic pain problem (as defined by ICD-11 (35); (3) having internet access; (4) having an iOS- or Android-based mobile phone; (5) a parent willing to participate in the study; and (6) providing informed consent/assent. Potential participants will be *excluded* if they have cognitive or language problems that could interfere with the correct understanding of the procedure and the questionnaires that will be used. Participants will not be restricted from engaging in concomitant interventions.

In the *usability study*, as recommended (28), participants will include 5 end users (i.e., adolescents with chronic pain) per cycle, and 2 or 3 cycles are expected (*N* = 15).

In the evaluation study, the recruitment of participants will take place at the 8 following Spanish hospitals: Hospital Universitario Infantil Niño Jesus, Hospital Sant Joan de Déu, Hospital Universitario La Paz, Hospital de Sant Pau i Santa Tecla, Hospital Universitario Miguel Servet, Hospital Universitari Son Espases, Hospital Universitari Vall d'Hebron, and Hospital Universitario 12 de Octubre. Hospital representatives will distribute informational brochures to adolescents and their families, outlining the details of the project and providing our contact information. This ensures that those interested can easily initiate direct communication with the research team.

Referred adolescents and their parents will sign informed consents or assents, as appropriate, if interested in participating. This involves providing a document describing in detail the study procedures and risks to interested adolescents and parents. This procedure has been described in the documents provided to the Human Subjects Ethics Committee of the Universitat Rovira i Virgili and approved by that Committee (CEIPSA-2023-PR-0033). If the adolescent and parent are willing to participate, they will sign the electronic informed consent/assent document prior to any study-related activity (36). The document will then be received by the Principal Investigator and authorized members of the research team.

In this study, the sample will include adolescents with chronic pain and one of their parents. Based on a within-subjects repeated measures ANOVA with three time points (baseline, post-treatment, and 3-month follow-up), we will use GPower (version 3.1.9.7) to calculate the required sample size. We set a small effect size (f = 0.10), with a two-tailed alpha of 0.05 and power of 0.80. For the calculation, the following parameters were assumed: number of measurements = 3 (baseline, post-treatment, and 3-month follow-up), correlation among repeated measures = 0.5, and nonsphericity correction epsilon = 1. This calculation indicated that a sample of *N* = 163 dyads would be sufficient. However, in order to prevent attrition issues, we will be recruiting a minimum of 195 dyads -minimal attrition is expected based on prior studies on digital treatments with similar populations (37). Recruitment is expected to proceed at a rate of approximately 5 participants per month, based on projections from similar previous studies [e.g., (30)]. To account for potential variability, we conservatively estimate a recruitment rate of 2 adolescents per month per hospital. With 8 hospitals participating, this would result in enrolling the required sample of 352 participants within 22 months. An additional 5 months will be allocated for participants to complete the treatment (approximately 8 weeks, as previously described) and the 3-month follow-up, bringing the total duration for recruitment, enrollment, and follow-up to 27 months.

In order to ensure that the target sample size is reached in the evaluation study, the following strategies will be implemented: (a) using clear and engaging messages (i.e., developing age-appropriate, visually appealing recruitment materials, like posters, flyers, or videos to be shared by hospitals and healthcare professionals); and (b) highlighting the benefits of participation, such as improving their own pain management and contributing to advancements in adolescent healthcare. Moreover, we will offer both monetary and non-monetary incentives (i.e., certificates of participation and feedback on their progress). To enhance participant retention and ensure completion of follow-ups, we plan to implement personalized reminders. These reminders will be delivered via app notifications, SMS, or email, and will serve to notify participants of upcoming tasks or scheduled follow-up activities.

We also plan to collect key outcome data from participants who discontinue or deviate from the intervention protocol to minimize data loss and reduce bias, both using direct (i.e., exit survey and interviews to capture feedback and reasons for withdrawal) and indirect or passive data collection procedures (i.e., using app analytics to record usage patterns and adherence metrics prior to discontinuation).

In this project, all participants will be compensated for their participation.

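### Section 2.3's recruitment figures contradict each other: the rate called conservative (16 per month) is 3.2 times the expected 5 per month, and the 22 months serve a required sample of 352 that matches neither 163 nor 195

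*Protocol article*

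**What the plan says.** All the figures stand in one paragraph of section 2.3 (Participants) of the protocol article.

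- **Sample size.** For a one-group repeated measures ANOVA with three time points: "We set a small effect size (f = 0.10), with a two-tailed alpha of 0.05 and power of 0.80", with "correlation among repeated measures = 0.5, and nonsphericity correction epsilon = 1". The result is "This calculation indicated that a sample of *N* = 163 dyads would be sufficient". To allow for attrition, which is expected to be minimal, at least 195 dyads are to be recruited.
- **Expected rate.** "Recruitment is expected to proceed at a rate of approximately 5 participants per month, based on projections from similar previous studies".
- **Rate used for planning.** "To account for potential variability, we conservatively estimate a recruitment rate of 2 adolescents per month per hospital".
- **Timeline.** "With 8 hospitals participating, this would result in enrolling the required sample of 352 participants within 22 months". Five further months cover treatment and the 3-month follow-up, "bringing the total duration for recruitment, enrollment, and follow-up to 27 months".

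The eight hospitals are named in the same section.

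**The concern.** A conservative planning rate should lie at or below the expected rate. Here it is higher than the only expectation given, and the expectation drawn from previous studies plays no part in the timeline. The number that the timeline is built to reach, 352, is called the required sample, although the sentences just before it give 163 as sufficient and 195 as the recruitment minimum.

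What is at stake is whether the study can be done in the time stated. From this paragraph an ethics committee, a funder or a participating hospital cannot tell which of two situations applies. Either the target is reached with many months to spare, or the study will run well beyond its stated duration. Nor can they tell how many adolescents are to be enrolled. Section 3.2 (Limitations) itself lists recruitment first among the anticipated challenges.

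**Working it through.** **Inputs (all from section 2.3).** Expected rate 5 per month; planning rate 2 per month per hospital; 8 hospitals; 22 months of recruitment plus 5 months; 163 dyads computed; minimum 195 dyads; required sample 352; f = 0.10, alpha 0.05, 3 measurements, correlation 0.5, epsilon 1.

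**1. Reproduce the plan's own figures.**
- Accrual: 2 × 8 = 16 per month; 16 × 22 = 352; 22 + 5 = 27 months. All agree with the article.
- Sample size: noncentral F with λ = N × 3 × f² / (1 − 0.5) = 0.06 N, df1 = 2, df2 = 2(N − 1). At N = 163, λ = 9.78 and power is 0.802; at N = 162 power is 0.7998. So 163 is the smallest N reaching 80%, as stated.

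**2. Compare the rates.** 16 / 5 = 3.2. With 5 read as study-wide, as it is written, the rate labelled conservative is more than three times the expectation.

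**3. Compare the samples.**
- 352 / 195 = 1.8 and 352 / 163 = 2.2.
- Attrition does not explain 352. Ending at 163 from 352 would mean a loss of 1 − 163/352 = 54%, whereas 195 implies 1 − 163/195 = 16.4%.
- Counting parents as well as adolescents does not explain it either. 352 / 2 = 176 dyads, which is neither 163 nor 195, and the rate that produces 352 is expressed in adolescents.

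**4. Timeline for each rate.**

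| Rate | Enrolled in 22 months | Months to 195 | Total with 5 months added | Months to 352 |
|---|---|---|---|---|
| 5 per month, study-wide | 110 | 39.0 | 44 | 70.4 |
| 16 per month | 352 | 12.2 | 17.2 (18 if rounded up to 13 + 5) | 22.0 |
| 40 per month (5 per hospital) | 880 | 4.9 | 9.9 | 8.8 |

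The 22 months fit only the pair of 16 per month and 352. To enrol 195 in exactly 22 months the rate would be 195 / 22 = 8.9 per month, a figure that appears nowhere.

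**5. Power, only on the condition that recruitment stops at 22 months at 5 per month.**
- 5 × 22 = 110 enrolled. With no loss, λ = 6.6 and power is 0.62.
- With the 16.4% loss implied by 195 to 163, 110 × 163/195 = 92 remain and power is about 0.54.

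**The case against.** **The 5 may be meant per hospital.** The expectation would then be 40 per month, and reducing 5 to 2 per hospital would be a genuine conservative step. This is the one reading on which the word conservatively makes sense, and it removes the rate contradiction. It stands as a possibility, but the text attaches the per-hospital unit only to the 2. It also leaves the second conflict in place: 22 months at 16 per month gives 352, not 195.

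**The study is not shown to lose power.** A reader might infer that at 5 per month the window closes with 110 adolescents and that the study delivers 54 to 62% power instead of 80%. The article does not support that as a plain consequence. It fixes a minimum of 195 dyads, words the 22 and 27 months as projections, lists strategies for reaching the target, and gives a contingency plan for recruitment in section 3.2. No sentence says that recruitment ends at 22 months regardless of enrolment. With the sample fixed, a slower rate costs time. The 54% figure needs a second assumption, a 16.4% loss, where the article expects minimal attrition. On the other side, no extension is planned either, so the article leaves open what would happen.

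**It cannot be shown that 16 per month is optimistic.** The 5 per month rests on previous studies whose number of sites the article does not give. Eight hospitals may well recruit faster. This stands: the finding is that the two stated rates conflict, not that 16 is unattainable.

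**The analysis is untouched.** The computed 163 is correct for its inputs, and no test or outcome changes. That is so, and it limits the weight of the point.

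**Conclusion.** The point holds as an internal contradiction in stated figures. Two conflicts need separating.

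- **Sample conflict, certain on every reading.** The required sample of 352 disagrees with 163 and with 195. This is the reason that 22 months does not fit the 195 target.
- **Rate conflict, certain on the literal reading.** The conservative 16 per month is 3.2 times the expected 5 per month. It disappears if 5 is per hospital, which the article does not say.

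For 195 dyads the total duration is about 18 months at 16 per month and 44 months at 5 per month study-wide, against the stated 27. These totals assume constant accrual and the article's own 5-month allowance. The supported consequence is an unreliable timeline, with a possible overrun of 44 − 27 = 17 months. Lost power (62% at most, about 54% with the implied attrition) follows only under a hard stop at 22 months, which the article does not state. The correction is cheap and concerns figures on which the study's feasibility rests, so it should be made.

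**What to change.** In the sample size paragraph of section 2.3:

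1. State whether the 5 participants per month is study-wide or per hospital.
2. Replace 352 with the actual recruitment target, 195 dyads, or justify 352 and reconcile it with 163 and 195. Check the projected numbers in the Consort diagram (Figure 3) against the same target.
3. Recompute the timeline for that target. For 195 dyads: 13 + 5 = 18 months at 16 per month, and 39 + 5 = 44 months at 5 per month study-wide.
4. If 5 is study-wide, present it as the conservative case and drop the word conservatively from the 16-per-month rate. If it is per hospital, say so; the word may then stay.
5. Say whether recruitment continues until 195 dyads are enrolled or stops at a fixed date. Only if it stops at 22 months regardless, add that 5 per month would give about 110 enrolled and at most about 62% power, or about 54% with the attrition implied by 195 to 163.

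The cost is the rewording of one paragraph, with the registry entry and Figure 3 brought into line if they carry the same numbers. The sample size calculation and the analysis need no change. The stated duration may become longer or shorter depending on the answer to item 1.
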